| To determine the impact of a generic paediatric patient reported outcome measure (P-PROM) on patient - clinician communication in routine outpatient care at The Royal Children's Hospital.                  | Patient - clinician communication. Based on patient/caregiver report to a study designed Likert question in the 1-day follow-up survey                                                                                                                                                                                                                      |
| To determine the impact of a generic paediatric patient reported outcome measure (P-PROM) on child quality of life .                                                                                         | Improvements in child health related quality of life, measured using the CHU9D (Appendix B) and based on change between baseline and 4-week follow-up. [7, 8]                                                                                                                                                                                               |

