## 4 TRIAL DESIGN

[figure not shown]

This study is a pilot feasibility and acceptability, non-blinded, randomised control trial (RCT). It is a pilot study because it is the first of its kind to assess a generic P-PROM intervention in routine clinical outpatient care in Australia across a range of clinical contexts and using a generic PROM called the EQ-5D-Y-5L. Hence it is essential to first conduct this pilot study to ensure the intervention is feasible, acceptable and demonstrates some effectiveness in routine clinical care before conducting a full-scale RCT.

A parallel group RCT methodology with an intervention and control arm will be utilised. Participants (children) will be randomly allocated to the intervention and control arm at a 1:1 ratio. An RCT methodology is being employed as it is the gold standard method for assessing the effectiveness of an intervention on an outcome.[9] RCT's balance participant characteristics (both observed and unobserved) between the two study arms, allowing attribution of any differences in outcome to the study intervention, which is not possible with any other study design.[9] An Intention-to-treat (ITT) analysis will be utilised, whereby all participants who are randomized are included in the statistical analysis and analysed according to the group they were originally assigned, regardless of what intervention (if any) they received.

Participants allocated to the intervention arm will receive the study intervention (see details below). Participants allocated to the control arm will receive standard care from their treating clinician at The Royal Children's Hospital at their outpatient clinic appointment.

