## **7 RANDOMISATION AND BLINDING**

Randomisation will occur after completion of the baseline survey. Randomisation will be performed by a person independent to the study. Block randomization will be employed with the goal of ensuring balance between study arms. The randomisation schedule will be created by computer-generated random numbers, before the first participant has been recruited. The schedule will be held by an independent person, and allocation will not be revealed prematurely to CI. Because of these procedures, the research team will be unable to predict which group the participant will be allocated to. Once participants have been randomly allocated to either the intervention or control arm they will be informed about this via an email from the research team. This email will also include instructions for what to expect next. The study arm a participant is allocated to will be logged in both REDCap and EPIC.

This pilot RCT will be non-blinded, meaning children/their caregiver(s), treating clinicians, and researchers (including those tasked with data collection and analysis) will be aware which study arm each participant has been allocated to. A non-blinded methodology was chosen as a placebo was not feasible or practical in this pilot trial.

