### **10.4 Methods of analysis**

As this is a pilot trial, most analyses are descriptive.

| OUTCOME                                                                                                                                                                                                                            | METHOD OF ANALYSIS                                                                                                                                                                                                                                                                                                                                                                                                               |
|------------------------------------------------------------------------------------------------------------------------------------------------------------------------------------------------------------------------------------|----------------------------------------------------------------------------------------------------------------------------------------------------------------------------------------------------------------------------------------------------------------------------------------------------------------------------------------------------------------------------------------------------------------------------------|
| Acceptability and feasibility.                                                                                                                                                                                                     | 
Most acceptability and feasibility outcomes will be assessed using descriptive statistics.
 
For example, the proportion of patient/caregivers allocated to the intervention arm who completed the PROM will be described.
 
Some sub-group analyses maybe conducted where appropriate by PROM completion type (paper versus portal), appointment type (face to face versus telehealth), and outpatient clinic.
 |

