| Improvements in child health related quality of life, measured using the CHU9D and based on                                                                                                                                        | 
Descriptive & inferential statistics.
 
The mean difference and standard deviation of CHU9D total score between baseline and 4-week follow-up for participants in intervention
                                                                                                                                                                                                                                   |

| OUTCOME                                              | METHOD OF ANALYSIS                                                                                                                  |
|------------------------------------------------------|-------------------------------------------------------------------------------------------------------------------------------------|
| change between baseline and 4-week follow-up. [7, 8] | and control arm will be reported. Differences between participants in intervention and control arm will be assessed using a t-test. |

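### The CHU9D comparison is a t-test on change with no baseline adjustment; ANCOVA on the baseline score already collected would generally be more precise at no extra data cost

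*Protocol*

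**What the plan says.** The summary of objectives and outcomes in Protocol Section 3 defines the quality-of-life outcome as "measured using the CHU9D (Appendix B) and based on change between baseline and 4-week follow-up". It is the last of seven secondary objectives.

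Section 10.4 classes its analysis as both descriptive and inferential. The descriptive part is "The mean difference and standard deviation of CHU9D total score between baseline and 4-week follow-up for participants in intervention" and for controls. The inferential part is one sentence: "Differences between participants in intervention and control arm will be assessed using a t-test". Neither baseline CHU9D nor clinic is named as a covariate here or for any other between-arm comparison. Clinic appears in Section 10.4 only as a possible sub-group factor for the feasibility and acceptability outcomes ("appointment type (face to face versus telehealth), and outpatient clinic").

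On timing, Section 7 says: "Randomisation will occur after completion of the baseline survey". The baseline CHU9D score is therefore a true pre-randomisation covariate. Section 4 sets 1:1 allocation. Section 10.1 expects about 50 children per arm, sets no required number, and says that the outcome data are to feed the sample size calculations of later full-scale trials.

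**The concern.** Once a baseline score is in hand, there are two common ways to use it in a two-arm comparison. A t-test on change subtracts the whole baseline from the follow-up, which is a regression with the slope set to 1. ANCOVA estimates the slope from the data. Where the true slope is below 1, as regression to the mean usually makes it, subtracting the whole baseline adds noise. It also pushes the estimate in the direction opposite to any chance baseline difference between the arms.

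The protocol fixes the change-score t-test in its text, so this is not a detail left open for the SAP. At stake are the width of the interval for the CHU9D effect from about 100 children, and the usefulness of the reported SD for planning a later trial.

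**Working it through.** **Inputs from the protocol.** About 50 per arm (Section 10.1); 1:1 allocation (Section 4); baseline before randomisation (Section 7); t-test on change, no covariates (Section 10.4). The protocol states no power, significance level, effect size, SD or correlation, so there is no figure of its own to reproduce.

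**Assumptions.** Equal SD σ at baseline and 4 weeks; correlation r taken as 0.3, 0.5, 0.7 and 0.9.

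**Step 1, variance per child.**
- Change score: 2σ²(1 − r)
- ANCOVA residual: σ²(1 − r²)
- Ratio, ANCOVA to change: (1 − r²) / [2(1 − r)] = (1 + r)/2

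The confidence interval scales with the square root of the ratio. The number of children that the change-score t-test would need for the precision of ANCOVA with 100 is 100 divided by the ratio.

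| r | SD of change | ANCOVA residual SD | Variance ratio | Variance lower by | CI narrower by | Equivalent children |
|---|---|---|---|---|---|---|
| 0.3 | 1.18σ | 0.95σ | 0.65 | 35% | 19% | 154 |
| 0.5 | 1.00σ | 0.87σ | 0.75 | 25% | 13% | 133 |
| 0.7 | 0.77σ | 0.71σ | 0.85 | 15% | 8% | 118 |
| 0.9 | 0.45σ | 0.44σ | 0.95 | 5% | 3% | 105 |

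**Step 2, cost of estimating the slope.** With N = 100 this inflates the ANCOVA variance by a factor of about 1 + 1/(N − 4) = 1 + 1/96, or 1%. The ratios become about 0.66, 0.76, 0.86 and 0.96, so the gain remains at each assumed r.

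**Step 3, if the SDs differ.** Let the SDs be s₀ (baseline) and s₁ (4 weeks). The variance of change minus the ANCOVA residual variance is s₀² + s₁² − 2r·s₀·s₁ − s₁²(1 − r²) = (s₀ − r·s₁)². This is never negative. It is zero when the slope r·s₁/s₀ equals 1, for example at r = 0.8 and s₁/s₀ = 1.25. The gain therefore depends on the slope, not on the correlation alone.

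**Step 4, chance baseline difference.** With 50 per arm the difference in baseline means has SD σ√(2/50) = 0.20σ, so it exceeds 0.2σ in either direction in about 32% of trials. Given a 0.2σ difference, the change-score estimate is shifted by −(1 − r) × 0.2σ: −0.14σ, −0.10σ, −0.06σ and −0.02σ for the four correlations. At r = 0.5 the standard error of the t-test estimate is 1.00σ × 0.20 = 0.20σ, so the shift is half a standard error.

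**Step 5, validity.** In simulations with 100 children, four clinics, r of 0.5 or 0.7, and 3,000 runs per setting, the change-score t-test rejected a true null in 4% to 5% of runs at a nominal 5%. Its mean estimate was on target.

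**Step 6, adding clinic.** In the same simulations, adjusting for baseline and clinic together gave variance ratios of about 0.73 (r = 0.5) and 0.80 (r = 0.7) under an assumed clinic variance of 0.1σ². With no clinic effect they were about 0.78 to 0.79 and 0.88 to 0.91, slightly worse than baseline alone. Clinic helps only if it predicts the outcome.

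**The case against.** The t-test on change is a legitimate analysis. In a 1:1 randomised trial it is unbiased over repeated randomisations and holds its type I error. The outcome is secondary, the trial has no power target, most of its analyses are descriptive, and no progression rule depends on this p-value. All of this stands, and it limits the weight of the point. It does not remove it: the comparison is labelled inferential, and a more precise analysis needs no data beyond what is already collected.

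The sample-size argument also has a limit. Section 10.1 does not say that the SD of change will be the planning value, and both SDs and the correlation can be computed from the same dataset whichever test is run. A later trial would be oversized (by 1/0.75 = 1.33 times at r = 0.5) only if it planned ANCOVA with the SD of change. That is a reason to report the correlation and residual SD, not evidence of an error.

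Stronger readings that a reader might infer, and that the documents do not support:
- *Chance imbalance in baseline CHU9D is ignored.* It is not. The change score uses the baseline; when the slope is below 1 it over-corrects.
- *ANCOVA gains at every correlation below 1.* That needs equal SDs (Step 3), and the protocol gives none.
- *The arms will be unbalanced by clinic.* Section 7 says "Block randomization will be employed with the goal of ensuring balance between study arms" and is silent on strata and block size. Section 4 lets trial dates differ between clinics, so the size of any imbalance depends on an unstated recruitment order. Nothing shows that clinic predicts CHU9D change.
- *All between-arm comparisons need covariates.* The argument here rests on a baseline CHU9D score and does not carry over to the chi-squared comparisons.

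**Conclusion.** The point holds as a matter of precision, not validity. Section 10.4 fixes an analysis that is generally less precise than ANCOVA on a score measured before randomisation. Under equal SDs the loss runs from small (5% of variance at r = 0.9) to substantial (35% at r = 0.3), and a chance baseline difference leaves the estimate shifted the opposite way. The correlation and the equal-SD condition are assumptions; if the true slope were 1 there would be no gain. Section 10.3 lets unanswered items stay missing, so the baseline score may not be complete for every child, but a missing baseline affects the change score equally. The weight is moderate, for a secondary outcome of a pilot.

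**What to change.** In Section 10.4, replace the t-test for CHU9D by a linear model of the 4-week score on arm and baseline score. Clinic may be added as a covariate, if that is decided before the data are seen. Report:
- the adjusted mean difference with its 95% CI;
- the residual SD;
- the correlation between baseline and 4-week scores.

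Keep the mean change and SD by arm as description. The summary of outcomes in Section 3, which words the outcome as "based on change between baseline and 4-week follow-up", can stay if Section 10.4 says that the arms are compared on the 4-week score adjusted for baseline.

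The cost is a short rewording of one table entry, with no new data, visits or participants, and about 1% of variance for estimating the slope.

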## 10.5 Interim Analyses

One week into the trial period, the proportion of participants who have complete the generic P-PROM (if allocated to intervention arm) will be computed as well as the proportion of time the clinicians are opening the generic P-PROM result on the EMR (if patient allocated to intervention arm). These interim results will be fed back and discussed with participating outpatient clinics.

## 11 ETHICAL CONSIDERATIONS

### 11.1 Research Ethics Approval & Local Governance Authorisation

This protocol and the informed consent document and any subsequent amendments will be reviewed and approved by the human research ethics committee (HREC) prior to commencing the research. A letter of protocol approval by HREC will be obtained prior to the commencement of the trial, as well as approval for other trial documents requiring HREC review.

### 11.2 Amendments to the protocol

This trial will be conducted in compliance with the current version of the protocol. Any change to the protocol document or Informed Consent Form that affects the scientific intent, trial design, participant safety, or may affect a participants willingness to continue participation in the trial is considered an amendment, and therefore will be written and filed as an amendment to this protocol and/or informed consent form. All such amendments will be submitted to the HREC, for approval prior to being implemented.

### 11.3 Protocol Deviations and Serious Breaches

All protocol deviations will be recorded in the participant record (source document) and on the CRF and must be reported to the Site Principal Investigator, who will assess for seriousness.

Those deviations deemed to affect to a significant degree rights of a trial participant or the reliability and robustness of the data generated in the clinical trial will be reported as serious breaches. Reporting will be done in a timely manner (Site Principal Investigator to report to the Sponsor-Investigator within 72 hours and to the Site RGO within 7 day; Sponsor-Investigator to review and submit to the approving HREC within 7 days).

Where non-compliance significantly affects human participant protection or reliability of results, a root cause analysis will be undertaken and a corrective and preventative action plan prepared.

Where protocol deviations or serious breaches identify protocol-related issues, the protocol will be reviewed and, where indicated, amended.

### 11.4 Risk mitigation

| Risk | Level of risk and justification for this categorisation | Mitigation strategies | Safety monitoring strategies & responses |
|------|---------------------------------------------------------|-----------------------|------------------------------------------|
|      |                                                         |                       |                                          |

|                                                                                                                                                                                                                  |                                                                                                                                                                                                                                                                                                                                                                                                                                                                                                                                                                                                                                                                    |                                                                                                                                                                                                                                                              |                                                                                                                                                                                                                                                                                                                                                                                                                      |
|------------------------------------------------------------------------------------------------------------------------------------------------------------------------------------------------------------------|--------------------------------------------------------------------------------------------------------------------------------------------------------------------------------------------------------------------------------------------------------------------------------------------------------------------------------------------------------------------------------------------------------------------------------------------------------------------------------------------------------------------------------------------------------------------------------------------------------------------------------------------------------------------|--------------------------------------------------------------------------------------------------------------------------------------------------------------------------------------------------------------------------------------------------------------|----------------------------------------------------------------------------------------------------------------------------------------------------------------------------------------------------------------------------------------------------------------------------------------------------------------------------------------------------------------------------------------------------------------------|
| Psychological distress from completing the generic PROM (i.e., the intervention), whereby the questions on the PROM cause the person completing the PROM distress.                                               | 
Low risk, unlikely to occur.
 
Based on a recent study where 760 children aged 5-18 from The Royal Children's Hospital completed the same PROM, EQ-5D-Y-5L, no adverse events from completing the PROM were reported.[11] Additionally, during qualitative interviews conducted in preparation for this trial, no adolescents or caregivers reported concerns regarding questions included on the PROM and all stated they would feel comfortable answering these questions prior to their appointment and having their answers discussed in the outpatient appointment with the clinician (work done as part of a pre-trial study - RCH HREC #92769).
 | Resources provided to families and clinicians to help address any health concerns that arise from completing generic P-PROM.                                                                                                                                 | 
Question included in 1-day follow-up regarding if any distress from completing generic PROM.
 
Clinicians will notify research team if they see any patient who demonstrate signs of distress from completing generic P-PROM. The PI will then follow-up with the participant to ensure their safety and may ask the paediatrician CI to follow-up with the participant if there are concerns remaining.
 |
| Time or cognitive burden on patients to complete PROM or take part in interview.                                                                                                                                 | 
Low risk, unlikely to occur.
 
Based on a recent study where 760 children aged 5-18 from The Royal Children's Hospital completed the same PROM, EQ-5D-Y-5L, the average completion time was 37 seconds and less than 3% reported the PROM as 'very difficult' to complete, indicating minimal time or cognitive burden.[12]
                                                                                                                                                                                                                                                                                                                            | 
Compensate families with \$20.
 
Participants able to complete PROM or take part in interview at a time that best suits them.
                                                                                                                    | 
Question included in 1-day follow-up regarding how easy or difficult they found completing the generic P-PROM.
 
Participants will be notified they can stop the interview at any time if it becomes too burdensome.
                                                                                                                                                                                     |
| Clinician not reviewing PROM result. A potential risk is that a patient or their caregiver completes the generic P-PROM and the clinician does not review this result. This may result in the patient being left | Low risk, moderate chance of occurring.                                                                                                                                                                                                                                                                                                                                                                                                                                                                                                                                                                                                                            | 
Strategies to minimise a clinician not reviewing a PROM result will be a key aspect of the implementation.
 
Furthermore, providing resources to patients and their caregivers on how they can address any health concerns arising from the PROM
 | The proportion of unopened generic P-PROM results in EPIC will be reported as an outcome of the trial.                                                                                                                                                                                                                                                                                                               |

|                                                                                                                                                                                                                                                                       |                                                                                                                                                                                                                                                                                                                                                                                                                                                                                                                                                               |                                                                                                                                                                                                 |                                                                                   |
|-----------------------------------------------------------------------------------------------------------------------------------------------------------------------------------------------------------------------------------------------------------------------|---------------------------------------------------------------------------------------------------------------------------------------------------------------------------------------------------------------------------------------------------------------------------------------------------------------------------------------------------------------------------------------------------------------------------------------------------------------------------------------------------------------------------------------------------------------|-------------------------------------------------------------------------------------------------------------------------------------------------------------------------------------------------|-----------------------------------------------------------------------------------|
| with an unmet health need that was identified on the generic P-PROM.                                                                                                                                                                                                  |                                                                                                                                                                                                                                                                                                                                                                                                                                                                                                                                                               | themselves will also be key.                                                                                                                                                                    |                                                                                   |
| Caregivers seeing PROM results completed by their child or young person, where they were expecting to keep these results private. There is a potential risk that some children or young people completing the PROM may not want their caregiver to see these results. | Low risk, unlikely to occur.

When this was discussed with adolescents in the qualitative interviews and co-design workshops done in preparation for this trial, it was felt that most younger children and younger adolescents would be happy for their caregiver to see these PROM results (work done as part of a pre-trial study - RCH HREC #92769). However, older adolescents, aged 16 years and above were felt to be more likely to want these results to remain private or to be made aware if their caregiver was going to see these results. | We will notify children, young people and their caregivers in the study information form as well as directly prior to them completing the generic P-PROM who will be able to see their answers. | Participants reporting to research team or clinicians this was an issue for them. |

